## Abstract

**Background:**

The global burden of acute malnutrition among children remains high, and prevalence rates are highest in humanitarian contexts such as Niger. Unconditional cash transfers are increasingly used to prevent acute malnutrition in emergencies but lack a strong evidence base. In Niger, non-governmental organisations give unconditional cash transfers to the poorest households from June to September; the ‘hunger gap’. However, rising admissions to feeding programmes from March/April suggest the intervention may be late.

**Methods/design:**

This cluster-randomised controlled trial will compare two types of unconditional cash transfer for ‘very poor’ households in ‘vulnerable’ villages defined and identified by the implementing organisation. 3,500 children (6–59 months) and 2,500 women (15–49 years) will be recruited exhaustively from households targeted for cash and from a random sample of non-recipient households in 40 villages in Tahoua district. Clusters of villages with a common cash distribution point will be assigned to either a control group which will receive the standard intervention (*n* = 10), or a modified intervention group (*n* = 10). The standard intervention is 32,500 FCFA/month for 4 months, June to September, given cash-in-hand to female representatives of ‘very poor’ households. The modified intervention is 21,500 FCFA/month for 5 months, April, May, July, August, September, and 22,500 FCFA in June, providing the same total amount. In both arms the recipient women attend an education session, women and children are screened and referred for acute malnutrition treatment, and the households receive nutrition supplements for children 6–23 months and pregnant and lactating women. The trial will evaluate whether the modified unconditional cash transfer leads to a reduction in acute malnutrition among children 6–59 months old compared to the standard intervention. The sample size provides power to detect a 5 percentage point difference in prevalence of acute malnutrition between trial arms. Quantitative and qualitative process evaluation data will be prospectively collected and programme costs will be collected and cost-effectiveness ratios calculated.

**Discussion:**

This randomised study design with a concurrent process evaluation will provide evidence on the effectiveness and cost-effectiveness of earlier initiation of seasonal unconditional cash transfer for the prevention of acute malnutrition, which will be generalisable to similar humanitarian situations.

**Trial registration:**

ISRCTN25360839, registered March 19, 2015.

## Background

Over one fifth of countries have a prevalence of acute malnutrition^1^ of 10 % or more, which is classified as “a public health emergency requiring immediate intervention” [1]. Humanitarian disasters may exacerbate pre-existing causes of undernutrition or create new risks, causing the prevalence of acute malnutrition to rise. Evidence exists on the effectiveness of food-based interventions for the treatment of severe acute malnutrition and moderate acute malnutrition [2], but their coverage is low [3] and costs are high [4].

Preventative interventions are also necessary and a range of sectoral activities may be required to tackle the multiple potential causes of undernutrition, including insufficiencies in household food security and diet, challenges in the social and care environment, and disease and a poor public health environment. Amongst these potential interventions, food-based approaches such as General Food Distributions (GFD) and Blanket Supplementary Feeding Programmes (BSFP) predominate. There is, however, limited evidence of their positive impact [5], critical challenges associated with their implementation [6, 7] and concerns about their cost-effectiveness [8].

As a consequence of the limitations of food aid, other forms of food assistance, such as short term cash and voucher interventions, have become more commonly used to try and prevent acute malnutrition in emergency situations in recent years [9]. But, whilst cash/vouchers have the potential to address various causes of undernutrition [10], there is limited and inconsistent evidence on their nutritional impact and little knowledge about which of the impact pathways may be influenced in different contexts.

Studies have shown that cash or vouchers can impact positively on diets and food security at a household level [11], however, little is known about their impact at an individual level. Similarly, evidence from longer term conditional cash transfers has shown that they can improve uptake of health services where services are available. However, this improved care-seeking does not often translate into improved health or nutrition outcomes [11].

Furthermore, it is generally agreed that implementation of cash/voucher programmes as stand-alone interventions are less likely to be efficacious, regardless of the different pathways by which they may impact nutrition status [12–14]. Understanding when cash and vouchers can work to reduce malnutrition and when and what other complementary interventions are required for effectiveness remains a research priority.

Seasonal Unconditional Cash Transfers (UCT) have been implemented by non-governmental organisations (NGO) in Niger since 2004 as a part of humanitarian programming. However, studies or evaluations undertaken to assess their nutritional impact have yielded inconsistent and inconclusive results [15–22]. Questions on the most effective timing, amount, and duration remain unanswered. It has become common practice to deliver cash from June to September to coincide with the annual ‘hunger gap’. However, monthly trends in the admission of acutely malnourished children to feeding programmes indicate that changes in incidence may not coincide with this lean season, with admission rising from March/April and again in September. There is also an absence of evidence on the impact of this economically targeted intervention at the population level.

This study aims to assess, on both targeted households and at the population level, the nutritional impact of a modified UCT that starts earlier in the year. It also aims to explore the pathways, shown in the REFANI theory of change (Fig. 1), by which the intervention may work, through changes in food security or other pathways. Lastly, the study will add to the sparse evidence base on the cost and cost effectiveness of cash transfer interventions. It is one of three studies undertaken by the REFANI consortium (the other two being in Pakistan and Somalia) with the common objective of enhancing understanding of the pathways by which cash and voucher transfers may work to reduce the risk of acute malnutrition in humanitarian emergencies.

**Fig. 1 Fig1:**
[figure not shown]
The REFANI studies theory of change

## Methods/design

### Objectives

To conduct a cluster randomised controlled trial (cRCT) of the effectiveness and cost-effectiveness of an earlier and longer (April-September) seasonal UCT intervention for preventing acute malnutrition in children 6–59 months of age, compared with the standard (June-September) seasonal UCT. Both UCT will be of equal total value and will target ‘very poor’ households in the Tahoua district of rural Niger. We will also conduct a process evaluation to describe the context and intervention implementation, and to explore pathways by which the intervention works or fails to work. This will inform judgements on the generalisability of the findings to other humanitarian contexts where cash transfers are being used to prevent acute malnutrition.

### Hypotheses

We have three hypotheses. 1. An earlier seasonal UCT, of equal value and longer duration than the standard intervention, reduces the prevalence of acute malnutrition in children aged 6–59 months, in the targeted ‘very poor’ households by the end of the lean season. 2. An earlier seasonal UCT, of equal value and longer duration than the standard intervention, reduces the prevalence of acute malnutrition in children, 6–59 months of age, in the communities in which the cash recipients live, by the end of the lean season. 3. The earlier seasonal UCT of equal total value to the standard intervention is more cost-effective per case of acute malnutrition averted compared to the standard intervention.

### Study setting and population

The study will be implemented in the communes of Affala and Takanamatt in the district of Tahoua in south west Niger where the NGO Concern Worldwide has been implementing multi-sector development and humanitarian assistance programmes since 2003. The majority ethnic group is Hausa, followed by Tuareg and Fulani. Agro-pastoral livelihoods and sedentary lifestyles predominate. The patriarchal culture is often associated with female disempowerment where male household heads are the main decision makers and control the majority of the household’s resources [23]. Literacy rates are very low, particularly among women [24].

There is a single short and unpredictable rainy season between June and September, which is also considered the ‘lean season’, which provides rain fed irrigation for millet, the staple crop. However, most households are unable to produce sufficient cereals for their own consumption, even in ‘normal years’ [25]. Households rely heavily on daily wage labour, labour migration, petty trade, taking credit and selling assets to maintain food access [25]. Besides food insecurity, challenges in the public health and social and caring environment, which are known risk factors for malnutrition, also exist. The environment is arid with a chronic lack of water, low coverage of latrines, and poor hygiene and sanitation practices are common [23]. Malaria is endemic and diarrhoea and acute respiratory infection rates are also high [23]. Despite the existence of free health care for children under five and pregnant women, geographic inaccessibility and the poor quality of the formal health service leads to low utilisation.

As a consequence of these challenges, nutrition surveys indicate that acute malnutrition prevalence 2 is persistently above 10 % in July, during the lean season, and is similar in the post-rains, post-harvest period in December. As well as working with government health services to treat children with acute malnutrition, Concern Worldwide implements multisector programmes to address the causes of undernutrition. These include seasonal cash transfers.

### Interventions

The selection of households that will be eligible to receive one of two UCT interventions will take place in a two stage process that is undertaken by Concern Worldwide as part of their normal humanitarian programming. First, villages will be targeted for UCT interventions based on their perceived vulnerability to food insecurity. Then, within the targeted villages, a wealth ranking is assigned to households using a household survey approach.^3^ This draws on the principles of HEA and has been standardised among NGOs in Niger [26]. Household with a very poor ranking are targeted for cash transfers.

The control intervention is a standard UCT package delivered by Concern Worldwide in Niger as a part of their humanitarian programmes. Each selected household receives 32,500 FCFA^4^ a month, which is given in cash to female representatives who must attend a cash distribution point every month, from June to September. Cash distribution points are sited in villages so that beneficiaries do not have to travel more than 5 km. The total seasonal cash transfer is 130,000 FCFA. The cash amount is calculated by the government to allow purchase of a food basket similar to the World Food Programme (WFP) household ration that will meet 75 % of the daily kilocalorie needs of a household of seven people. Cash is given to women on the assumption that they will be able to influence its use to the benefit of children. The cash transfer is manual because the mobile phone network does not support money transfers. A nutrition supplement is given to any pregnant and lactating women (PLW) and children 6–23 months old in the cash receiving household regardless of their nutritional status, as long as they attend on the distribution day. At the distribution, women must attend a health, hygiene, and nutrition education session and PLW and children are screened for acute malnutrition using Mid Upper Arm Circumference (MUAC) and referred to supplementary or therapeutic feeding programmes according to referral criteria. Concern Worldwide also undertakes community sensitisation on the objectives of the cash programme, including suggestions to use the cash to buy food for children.

The modified intervention gives the same total amount of cash to households, but over a longer period of time. A UCT of 21,500 FCFA is given manually to female household representatives who must attend a cash distribution point every month from April to September (22,500 FCFA is given in June). The total seasonal cash transfer is the same as for the standard intervention (130,000 FCFA). The intervention is the same as the standard intervention in all other ways and nutrition supplements are only given between June and September. Figure 2 illustrates the intervention components and timings, alongside the data collection plans.

**Fig. 2 Fig2:**
[figure not shown]
REFANI-N intervention and data collection schedule

### Study design and randomisation

The study design is a community-based, two-arm cluster RCT. We will assess the impact of UCT interventions on the risk of child undernutrition among households targeted for intervention and also in the community in which the interventions are implemented. A clustered design is necessary to ensure feasibility of delivery of the interventions being tested and to prevent contamination. The unit of randomisation will be the cash distribution point; i.e. one or more villages grouped to receive cash in a given location. Households will be assigned to the trial arm on the basis of their village of residence. The randomisation will be undertaken in a public meeting to which the village leaders will be invited. The names of the villages and their cash distribution point will be written on pieces of paper placed in sealed envelopes of identical shape size and colour. Meeting participants will be invited to blindly select envelopes one by one which will be sequentially allocated to the modified and standard cash arms, until all have been allocated. There will be around 20 cash distribution points, which will result in each intervention group having 10 clusters that will contain around 20 villages.

Cash receiving households will be exhaustively sampled from the selected villages for inclusion in the study cohort. In addition, a sample of households not eligible for cash transfers will be randomly sampled for inclusion in the cohort, from the same villages. The study participants will be children 6–59 months and women 15–49 years, exhaustively sampled from the selected households. The target number of participants is 3,500 children (6–59 months) and 2,500 women (15–49 years). Disabled and seriously sick individuals will be excluded.

Questions related to household costs and income will be included in the endline cohort questionnaire. For collection of qualitative data on household and community costs, up to 10 villages will be selected purposively using selection criteria (e.g. village size, whether village is located at a distribution point, remoteness of village, receipt of standard or modified intervention) to ensure a wide range of village characteristics are represented in the sample. Up to nine participants for the focus group discussions will then be selected randomly from amongst the programme beneficiaries in each village.

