### Sample size calculation

In order to detect a difference of 5 percentage points in the prevalence of acute malnutrition among children 6–59 months of age between the trial arms, assuming a fixed number of 20 clusters and end-line prevalence of 21 %, and allowing a type 1 error rate of 5 % and power of 80 %, we calculated that a minimum sample size of 1,767 children in 10 clusters for each arm will be necessary. Because the clustered sample design will induce correlation within sampling units, we used a sample size calculation method designed for use with clustered RCTs [28]. We also accounted for variable numbers of children served by each distribution point in calculating our final sample size.

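### Around 20 distribution points in two known communes are allocated by one unstratified draw; drawing within commune would remove a chance imbalance that costs precision, at almost no cost.

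*Protocol article*

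**What the plan says.** The protocol article, under Study setting and population, names two sites: "The study will be implemented in the communes of Affala and Takanamatt". Under Study design and randomisation the unit is a distribution point: "The unit of randomisation will be the cash distribution point; i.e. one or more villages grouped to receive cash in a given location". The number is approximate: "There will be around 20 cash distribution points, which will result in each intervention group having 10 clusters". The names go on paper "placed in sealed envelopes of identical shape size and colour", and then: "Meeting participants will be invited to blindly select envelopes one by one which will be sequentially allocated to the modified and standard cash arms", continuing until none is left.

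The article does not use the term single pool, but identical envelopes alternated between arms until exhausted leave no room for strata. The procedure fixes the number of clusters per arm and nothing else. Under Data analyses, the GEE allows for correlation within clusters, and covariates are to be chosen from the theory of change. Commune is not named there.

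**The concern.** Commune is known before the draw and is an obvious candidate stratum. With about 10 clusters per arm, an unrestricted draw can leave one commune over-represented in one arm. If prevalence of acute malnutrition differs between communes, part of that difference then sits inside the arm contrast of the one allocation that is realised. Averaged over all possible draws this is extra between-cluster variance. In the one draw that happens it is a shift that readers will see in the baseline table and may not be able to separate from the effect of earlier cash.

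The number of clusters is treated as fixed in the sample size calculation, so precision cannot be bought with more clusters. The draw is also the one step that a later analysis plan cannot change.

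**Working it through.** **Inputs from the protocol article.** Two communes (Study setting and population). About 20 clusters, 10 per arm, alternated from one set of envelopes (Study design and randomisation). Target difference 5 points, end-line prevalence 21%, type I error 5%, power 80%, 1,767 children per arm in 10 clusters (Sample size calculation).

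**Assumptions, not in the article.** Exactly 20 points; 10 per commune (other splits below); a commune difference D of 3 to 5 points; a two-sided test.

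**1. The plan's own figure.** The article gives no intracluster correlation (ICC) and no coefficient of variation of cluster size, so 1,767 can be back-solved but not reproduced. For 21% against 16%, two-sided, the usual two-proportion formula gives 946 per arm without clustering.
- Design effect = 1,767 / 946 = 1.87.
- Mean cluster size = 1,767 / 10 = 176.7.
- With equal clusters, ICC = 0.868 / 175.7 = 0.0049. With an assumed coefficient of variation of 0.3 to 0.7 it is 0.0045 to 0.0033. Reading the contrast as 21% against 26% gives 0.0032 with equal clusters.

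**2. Chance of imbalance.** Let k be the number of one commune's 10 points that fall in one arm. P(k) = C(10,k)² / C(20,10), with C(20,10) = 184,756.
- 5:5: 63,504 / 184,756 = 0.344.
- 6:4 either way: 2 × 44,100 / 184,756 = 0.477.
- 7:3 either way: 2 × 14,400 / 184,756 = 0.156.
- 8:2 or worse: 0.023.

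So 7:3 or worse has probability 0.156 + 0.023 = 0.179, and any imbalance 1 − 0.344 = 0.656. If the communes hold 8 and 12 points, a gap of four or more clusters between arms has probability 0.170; with 6 and 14 it is 0.141. A draw within commune gives no gap for even counts and at most one cluster for odd counts.

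**3. Effect on the contrast.** The shift is the difference in commune share between arms times D.
- 6:4: (0.6 − 0.4) × D = 0.2D, which is 0.6 points at D = 3 and 1.0 at D = 5.
- 7:3: (0.7 − 0.3) × D = 0.4D, which is 1.2 points at D = 3 and 2.0 at D = 5 (24% and 40% of the 5-point target).

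**4. Average loss of precision.** Var(k) = 10 × 0.5 × 0.5 × 10/19 = 1.316. The difference in share is (2k − 10)/10, with SD 2 × 1.147 / 10 = 0.229. The commune component of the arm difference therefore has SD 0.69 points at D = 3 and 1.15 at D = 5. The planned standard error is 5 / (1.96 + 0.84) = 1.79 points. If that planned error contains the component, its share of the variance is 0.69² / 1.785² = 15% at D = 3 and 1.147² / 1.785² = 41% at D = 5. Removing it would raise power from 0.80 to about 0.86 and 0.955 (normal approximation).

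**5. How large D can be.** With 10 points per commune, D alone produces a between-cluster SD of D/2. At an ICC of 0.0049 and the mean prevalence of 18.5%, the total between-cluster SD is √(0.0049 × 0.185 × 0.815) = 2.7 points, so D is at most about 5.5. At 21% the limit is 5.7; with a coefficient of variation of 0.7 it falls to about 4.5 to 4.7. A D of 8 would need an ICC of 0.04² / (0.185 × 0.815) = 0.0106, about twice the implied value. D = 5 already requires commune to account for (2.5 / 2.73)² = 84% of the between-cluster variance; D = 3 requires 30%. If the 5% type I error is one-sided, the implied ICC is 0.0078 and the limit loosens to about 6.9.

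**The case against.** The strongest reply is that nothing here is an error. A blind public draw is valid randomisation, and any unstratified covariate can be unbalanced by chance. The GEE allows for between-cluster variation, so the confidence interval already carries this uncertainty. That stands. A reader might infer that the draw biases the trial or inflates its type I error; the documents do not support that. Nor is commune variance an addition to the plan: whatever lies within the ICC used is already inside the 80% power. What the trial forgoes is a gain in precision.

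Second, the article reports no difference between the communes in malnutrition, access or delivery, and describes the setting as a whole. This also stands: D is an assumption. Gaps of 8 or 10 points do not fit the variance implied by the stated sample size.

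Third, the 0.66 probability of any imbalance sounds alarming, but 0.48 of it is a 6:4 split, which moves the contrast by only 0.2D.

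Fourth, a reader might infer that the distribution points are markedly unequal in size and that stratifying would cure this. The article says only: "We also accounted for variable numbers of children served by each distribution point". It gives no spread, and two piles do not balance size.

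Fifth, the Discussion section puts implementation as ongoing since March 2015, and the modified arm is paid from April, so the draw may be past. A baseline round and covariate adjustment are planned, and naming commune could be left to an analysis plan. This limits the remedy but does not remove the point, since adjustment is still open and the article does not commit to it.

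**Conclusion.** The point holds as an inexpensive improvement to a valid design. The article fixes one unstratified draw of about 20 clusters from two known communes. Under an assumed 10/10 split, a 7:3 or worse allocation has a probability of roughly one in six (0.18), or 0.14 to 0.17 for splits from 6/14 to 8/12. At 7:3 it shifts the contrast by 1.2 to 2 points for D of 3 to 5 points. The loss is in precision and in the credibility of the realised allocation.

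The size rests on three things that the article does not give: the number of points per commune, D, and the ICC, which is back-solved here under a two-sided test. The upper end, D = 5, is close to the most that the planning variance allows. If the communes do not differ, nothing is lost by the single draw.

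**What to change.** If the draw is still open, sort the sealed envelopes into two piles by commune and draw each to exhaustion at the same public meeting, alternating arms within the pile. If a commune has an odd number of points, start the second pile with the arm that is one short. Include commune as a fixed factor in the GEE so that the analysis matches the design.

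If the draw has taken place, report the number of distribution points per commune in each arm, and prespecify commune as a covariate before the end-line analysis. Adjustment recovers much of the precision, though not the visible balance.

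The cost is a second pile of envelopes and one between-cluster degree of freedom (17 instead of 18, which moves the two-sided 5% t quantile from 2.101 to 2.110). The change balances the number of clusters by commune. It does not balance the number of children or other village characteristics.
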